Within each school we will recruit 20 citizen scientists (total of *N* = 240) to measure pollution on their commute to and from school during parallel data collection periods across the 12 schools. Each pupil will carry the sensor for up to 5 days during each observation period, with data collected over 4 week observational periods within each school (a total of 20 days per pupil over 12 months). Atmotube Pro sensors (https://atmotube.com/products/atmotube-pro) which measure PM, volatile organic compounds (VOC), temperature and humidity, will be linked to a research smartphone which will also collect GPS tracks for their walk to and from school; these devices will be carried in a small waist/belt-bag. Children will be encouraged to engage in normal activity throughout the week. They will complete a short diary to record how they travelled to school, and locations visited each day. Detailed instructions and training will be given to pupils and parents.

Static sensors have been developed which use a Raspberry Pi Zero connected to two PM sensors: a Sensiron SPS30 PM sensor (which measures PM1, PM2.5 and PM10) and an Alphasense R2 optical particle counter which also gives more detailed particulate matter size information. Ambient temperature and relative humidity are also measured. Atmospheric data is logged every 10 seconds. Each school has the option to receive 3 static sensors; one outdoor and two indoor (one in a classroom and the other in a central location normally the dinner hall. All schools also have the option to receive a commercially available Purpleair PM2.5 sensors which displays data on a simple user friendly interface (https://map.purpleair.com/1/mPM25/a10/p2592000/cC0#10.89/53.7837/-1.7868) which is an effective tool for teaching and engagement. Triplicate NO_2_ tubes, which are changed monthly are installed at key outdoor locations for each school. A web dashboard to allow easy visualisation of pollution data collected via static and mobile sensors will be developed.

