#### Analysis methods

Routinely collected air quality data will be analysed by the DEFRA national evaluation team in parallel to the current evaluation and will allow an analysis of trends in air quality across the district. The approach estimates the time-varying background levels of air quality from the Automatic Urban and Rural Network (AURN) of continuous monitoring stations for any given time point, and subtracts these from locally measured air quality data at roadside locations so that the contribution and trends associated with local traffic and the implementation of the B-CAP can be identified. As air pollution levels vary with fluctuations in emissions and dispersing air-flows, the underlying changes can only be established by ‘de-weathering’ and ‘de-seasoning’ local data [55]. Any abrupt or gradual changes in these trends around the intervention date of the B-CAP will then be estimated using change point detection methods [56].

The DEFRA evaluation methods for processing data will be adapted to deal with the additional data collected across our 12 schools within our intensive observation period (mobile sensing with *n* = 240 citizen scientists) and extended observation periods (continuous monitoring from static sensors).

The personal exposure of school citizen scientists (*n* = 240) before and after the introduction of the B-CAP will be mapped onto a 500 m × 500 m grid centred on each school. Any difference in levels, over the under-lying trends (as determined by the DEFRA evaluation project), will be attributed as impacts of the B-CAP. If the intervention is successful, it is expected that any differences would be greatest for the schools located within the CAZ boundary; however, as the CAZ may influence overall traffic volume and traffic flow, the benefits may extend beyond the CAZ boundary. Our study design allows us to explore any dose-response relationships with schools located on CAZ boundaries and distal to the CAZ boundary. We will explore differences using a 2 (pre/post) × 3 (location: inside, bordering or distal to CAZ) design using the Friedman test. Data from personal sensors will also be used to create an ‘exposure index’ along key transit routes to and from schools, allowing us to explore impact of the B-CAP on exposure during the school commute.

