We will examine time-series line plots of the health outcomes to aid identification of underlying trends and seasonal patterns of the data. As the outcomes are counts, the Poisson link function will be used in the regression model. Models will be adjusted for age, sex, ethnicity, and measures of SES such as IMD. The coefficients from this regression can be used to estimate the intervention effect (the absolute difference between the predicted outcome based on the B-CAP and its counterfactual value, i.e. the expected values for level and trend if the intervention had not occurred. We will account for the disruption caused as a result of the COVID-19 pandemic, and the subsequent changes in behaviour including alterations to travel behaviour and A&E and GP attendances, through the selection of change points used in the segmented regressions. In England, the first lockdown was implemented on the 23rd of March 2020 and the third ended on the 31st July 2021. We will therefore consider four segments for our analysis: (1) the period prior to the first national lockdown from when clinical data of sufficient quality was available (October 2017 – March 2020); (2) the period spanning the lockdowns (March 2020 – August 2021); (3) the period encompassing the preparation phase for the CAZ (August 2021 - CAZ switch on, this includes other activities within the B-CAP including provision of grants for vehicle upgrades); (4) the period post ‘switch on’ of the charging CAZ). We will conduct an interim analysis at 12 months post-implementation and re-examine analyses 3 years post-implementation.

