Given the seasonal variation in respiratory outcomes and pollution, data will be adjusted for seasonality. We will also assess the models for residual autocorrelation and apply ARIMA methods as necessary. We hypothesize that the B-CAP will lead to a larger decrease in outcomes for those living in more deprived areas and by ethnicity and will examine these through interaction terms and stratified analyses. We will consider a series of sensitivity analyses by varying model assumptions. We expect air pollutants to decrease the most within the CAZ boundary compared to without and will examine the impact of spatial variation on outcomes. We will test our assumption that the effects of the implementation of the CAZ are gradual, by altering the length of the third segment based on dates of when implementation activities were initiated. We will also assess lagged effects between exposures to air pollution and health outcomes.

ITS is a strong evaluation design when randomization is not possible as post-intervention trends can be compared to trends prior to the interruption of the intervention. We will strengthen this design through the inclusion of a non-equivalent control (NEC) outcome (superficial head injuries) which will not be affected by the intervention (CAZ) to control for possible concurrent events. Previous studies utilizing a NEC have used finger wounds [31]); we chose superficial head injuries given the higher number of cases per month compared to other potential injuries. A change in the outcome of interest following implementation of the CAZ with no change in the NEC would increase our confidence that the changes observed were a result of the intervention.

For WP3B, we will conduct detailed analyses on health inequalities using data from the BiB cohort, which has individual, in addition to area level, information on socioeconomic status. We will replicate analysis on respiratory outcomes looking at both combined respiratory morbidities and separately at asthma/wheeze, exploring multi-dimensional measures of socio-economic status, [68] ethnicity, deprivation, employment, religion, education and social capital using the PROGRESS framework as a guide to selecting relevant indicators [57].

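### The WP3 health models name season but not weather, so the lagged pollution–attendance estimates risk confounding by within-season temperature and the switch-on terms carry weather error

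*Protocol article*

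**What the plan says.** All references are to the protocol article.

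- **Covariates** (Work package 3, Analysis methods): "Models will be adjusted for age, sex, ethnicity, and measures of SES such as IMD".
- **Season** (same section): "Given the seasonal variation in respiratory outcomes and pollution, data will be adjusted for seasonality".
- **Lagged analysis** (same section): "We will also assess lagged effects between exposures to air pollution and health outcomes". No model, exposure series, time unit or covariates are given for it.
- **Safeguards** (same section): "We will also assess the models for residual autocorrelation and apply ARIMA methods as necessary", and "We will consider a series of sensitivity analyses by varying model assumptions". Superficial head injuries serve as a control outcome, and spatial variation in relation to the CAZ boundary will be examined.
- **Pollution series** (Work package 2, Analysis methods): "the underlying changes can only be established by ‘de-weathering’ and ‘de-seasoning’ local data".
- **Effect sizes** (Power calculations): respiratory admissions rise 0.57–3.5% per 10 μg/m3 of NO2; the planned effect is a 5% reduction; power above 90% is claimed for a 2% reduction, from 312 weekly points and about 380 attendances a week in the pilot subsample.

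No weather variable appears anywhere in WP3, in the main models or in the sensitivity analyses.

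**The concern.** The article gives a reason for its seasonal term: season moves both respiratory outcomes and pollution. Weather plausibly has the same structure. WP2 says that air movement changes measured pollution, and cold, still spells plausibly raise respiratory attendances. A seasonal term takes out the expected value for the time of year. It does not take out the departure of a particular week from that value, and such departures are what a lagged pollution–health analysis uses.

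The demographic covariates that are named hardly change from week to week in a district-wide count, so they cannot stand in for weather. The lagged analysis is the only place where WP3 links measured pollution to attendances. If weather is left out of it, part of a reported NO2 association could be a temperature effect. Separately, an unusually cold or mild spell near switch-on would feed into the level and slope changes on which the health results rest.

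**Working it through.** The article states no figure on this point, so there is none to reproduce. The sizes below are illustrations. The weather inputs are assumptions, because the documents give none.

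**1. Lagged analysis: omitted-variable bias**

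Bias per 10 μg/m3 = 10 × ρ × (SD of temperature ÷ SD of NO2) × γ. Here ρ is the correlation of the weekly temperature and NO2 anomalies after removal of season, and γ is the proportional change in attendances per °C. Both are taken as negative, so the bias is positive.

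Assumed: temperature SD 2.5 °C, NO2 SD 6 μg/m3, ρ from −0.2 to −0.6, γ from −0.5% to −2% per °C.

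- Low: 10 × 0.2 × (2.5/6) × 0.5% = 0.4%
- Central: 10 × 0.4 × (2.5/6) × 1% = 1.7%
- High: 10 × 0.6 × (2.5/6) × 2% = 5.0%

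A second set of assumptions uses the same ρ, a weather effect of 1% to 3% per SD and an NO2 SD of 6 to 10 μg/m3:

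- Low: 10 × 0.2 × 1% ÷ 10 = 0.2%
- High: 10 × 0.6 × 3% ÷ 6 = 3.0%

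Together the range is about 0.2% to 5% per 10 μg/m3, against the cited 0.57–3.5%.

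**2. Segmented model: chance weather variation**

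The model has a level and a slope for each of the four planned segments and two annual harmonics. From the stated dates, segment 1 has 129 weeks and segment 2 has 71. Segment 3 runs from August 2021 to a 2022 date that is not given, so 22 to 74 weeks. Segment 4 has 156 weeks, or 52 at the interim analysis.

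Weekly temperature anomalies with SD 2.5 °C and lag-one autocorrelation 0.4 (assumed) were projected on the switch-on level term. With a third segment of 44 to 60 weeks:

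| Post-switch-on weeks | SD passed to the level change | At 0.5–2% per °C |
|---|---|---|
| 156 | 1.2–1.4 °C | about 0.6–2.7% |
| 52 (interim) | 1.5–1.7 °C | about 0.7–3.4% |

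**3. Segmented model: one anomaly at switch-on**

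An assumed 5% non-seasonal excess in the last 12 weeks before switch-on, with 156 weeks after it, gives:

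| Segment 3 (weeks) | Spurious level change | Spurious slope change per year |
|---|---|---|
| 22 | −6.6% | −17.4% |
| 40 | −4.7% | −8.2% |
| 56 | −3.6% | −4.7% |
| 74 | −2.8% | −2.9% |

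The same excess in the first 12 weeks after switch-on moves the level change by +1.2% to +1.4% with 156 post weeks, and by +3.7% to +4.1% at the interim. In a plain model with 156 weeks on each side, the excess before switch-on gives only −1.3%. Most of the sensitivity therefore comes from the short third segment.

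**4. Do the standard errors cover it?**

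In simulations with the inputs of step 2 and 380 attendances a week, the mean level estimate was close to zero, so stationary weather causes no systematic bias. With first-order autoregressive errors, 95% intervals covered in about 91–95% of runs. With an uncorrected Poisson fit, coverage fell to about 75% at the strong end of the assumed weather effect.

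**The case against.** **A condensed article may leave covariates to the analysis plan.** The lagged analysis is one sentence with no model, and the covariate list stands with the segmented regression. Nothing rules weather out. A reader might infer that the lagged estimates are confounded; the text supports only a risk of it. What remains is that the article does state an adjustment set, gives a reason for the seasonal term, and omits a variable to which the same reason applies.

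**WP2 and WP3 do not contradict each other.** A reader might take the WP2 sentence as a rule that WP3 breaks. It concerns pollutant concentrations in the national evaluation team's analysis, and the main segmented model has no pollution term. Nor is it said whether the lagged analysis would use raw or de-weathered pollution. This is an inconsistency of approach, no more.

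**In the segmented model, weather is mainly noise.** This stands largely: ARIMA errors, if applied, restore most of the coverage. They do not remove a single anomaly that falls at switch-on, and they do not deal with confounding in the lagged analysis. The head-injury control need not respond to weather as respiratory attendances do. A comparison inside and outside the CAZ would largely share the weather, but it is planned in addition to the district-wide before–after contrast and does not replace it.

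**The time unit.** A reader might infer that the lagged analysis will use weekly bins and so blur short lags. Weekly counts are set for the time-series outcome; no unit is stated for the lagged analysis.

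**The sizes are assumed.** True. The lagged bias spans a wide range, so it cannot be said how much of a future estimate would be temperature.

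**Conclusion.** The point holds as an improvement to a stated method. WP3 names season and omits weather, and a seasonal term cannot remove within-season temperature.

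For the lagged analysis the risk is confounding of about 0.2% to 5% per 10 μg/m3. That is the order of the association being sought, and it depends wholly on the assumed correlation, standard deviations and weather effect.

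For the segmented models the issue is mainly precision. Under the assumptions shown, chance weather adds an SD of about 0.6–2.7% to the level change at three years and 0.7–3.4% at the interim, against the 2% reduction described as detectable. It becomes an error in one direction only if an anomaly happens to fall near switch-on. The documents do not show that the segmented estimates are biased.

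**What to change.** In Work package 3, Analysis methods:

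- **Lagged pollution–health analysis:** prespecify temperature (non-linear, current and lagged) and humidity alongside season.
- **Segmented models:** include the same terms, at least as a named sensitivity analysis, at both the interim and the three-year analysis.
- **Source:** name a district meteorological series that covers the whole study period. The school devices, for which the article says "Ambient temperature and relative humidity are also measured", are not a substitute: they are optional, mostly indoors and tied to the school monitoring. De-weathering is done by the national team, and the article does not say that this team holds its meteorological data, so access has to be arranged.

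**Cost:** obtaining and merging the series, about three to six extra parameters, and a somewhat larger standard error for the NO2 coefficient. Before any gain from lower residual variance, the factor for a single linear temperature term is 1/√(1 − ρ²): 1.02, 1.09 and 1.25 for a correlation of 0.2, 0.4 and 0.6.

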### The Bradford Clean Air Plan

Bradford, a city of located in the North of England in the United Kingdom, has been identified by the UK government as having a number of locations where the average annual concentrations of NO_2_ exceed the statutory limit of 40 μg/m3. As a result, the local government in Bradford (Bradford Metropolitan District Council, referred to hereafter as Bradford council) has been mandated by central government to bring about compliance in the shortest possible time, including consideration of implementing a charging CAZ. In response to this ministerial directive, Bradford council has developed and secured funding for the Bradford Clean Air Plan (B-CAP) and started to implement some activities, including provision of grant funding for local businesses to upgrade taxis, buses, lorries, coaches and vans in late 2021. The full B-CAP, which includes a ‘class C’ charging CAZ (please see below for further details) is planned to go live in 2022. The plan was informed by Government guidance, extensive modelling, consultation with business (e.g. bus and taxi companies), communities, including bespoke work with ‘seldom heard’ and ‘underserved’ communities [35] and local councillors.

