#### Analysis methods

For WP3A, demographic information from cBradford (age, sex, ethnicity, IMD and geographic location (ward level of those inside and outside the CAZ)) will be summarised using frequency (%) or mean (SD). For WP3B, information (age, sex, ethnicity, IMD, measures of SES) from the BiB cohort will similarly be summarised. An interrupted time series (ITS) design using segmented regression analysis will be used to estimate levels and trends during specific points in time (segments), where the values of the time-series may change from the previous pattern because changes in air pollution trends as a result of the B-CAP intervention. In segmented regression, terms are included in the model to indicate, for example, the baseline level of the outcome, the implementation of the intervention, and time after the intervention. These effectively fit separate regressions for “segments” so that it is possible to estimate changes in level and trend. The assumption underlying our analyses is that we would expect a slope change in our outcome measure as we expect the implementation of the B-CAP and its effects are gradual.

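### Changing the length of the pre-switch-on segment cannot test whether the CAZ effect after switch-on is gradual or immediate

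*Protocol article*

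**What the plan says.** All references are to the Protocol article. Under Work package 3, Analysis methods, the stated assumption is that "we would expect a slope change in our outcome measure as we expect the implementation of the B-CAP and its effects are gradual".

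The same section sets the break points: "We will therefore consider four segments for our analysis". The second is "the period spanning the lockdowns (March 2020 – August 2021"; the third is "the period encompassing the preparation phase for the CAZ (August 2021 - CAZ switch on"; the fourth runs from switch-on. The text dates the end of the last lockdown: "the third ended on the 31st July 2021".

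The check on gradual effects is stated as follows: "We will test our assumption that the effects of the implementation of the CAZ are gradual, by altering the length of the third segment". The new length is to be "based on dates of when implementation activities were initiated". The only implementation activity with a date is in the Background section on the Bradford Clean Air Plan: "provision of grant funding for local businesses to upgrade taxis, buses, lorries, coaches and vans in late 2021". Other supporting measures, in Table 2, are undated. Switch-on is planned for 2022 without a day or month.

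The Follow-up section, by contrast, expects respiratory and cardiovascular attendances to fall immediately once the plan is in place, with legal compliance on air quality reached one year after implementation.

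**The concern.** The check and its purpose do not match. Whether the effect after charging begins is a step, a slope or a ramp shows only in the data after switch-on. The segment being varied lies wholly before it. If each segment has its own level and slope, changing where the third one starts leaves the fourth-segment data and fitted line as they were. Only the extrapolated counterfactual can change.

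The shape matters because the document leaves it open: Analysis methods expects a gradual change and Follow-up an immediate one. A check that gives the same answer under both could be reported as support for the gradual model. Any movement it did show could be read as evidence on how the zone works when it comes from the handling of lockdown weeks.

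**Working it through.** **Scale of the series.** The plan gives no figure for this check. The nearest is its power statement for weekly respiratory counts: above 90% for a 2% fall, with 312 weekly points and a mean of 380. A level-only Poisson comparison of 156 with 156 weeks (two-sided 5% assumed) has SE = √(1/59,280 + 1/58,094) = 0.00584. With |ln 0.98| = 0.0202, z = 3.46 and power = Φ(3.46 − 1.96) = 93.3%. The inputs below are on the plan's own scale.

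**Model.** Poisson regression of weekly counts with four segments: log μ(t) = baseline level and slope + a level change and a slope change at each break + season (where used). Effect at the end of year three = exp(level₄ + 3 × slope₄) − 1, with slope per year.

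**Assumed, not in the document:** a 40% lockdown drop, go-live on 4 July 2022 (26 September as the alternative) and the seasonal amplitudes. The 5% effect is the plan's own planning value.

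**Weeks reassigned.** From 2 August 2021, a third segment starting on 4 October leaves out 63/7 = 9 weeks; on 1 November, 91/7 = 13; on 6 December, 126/7 = 18. With four contiguous segments these weeks join the lockdown segment.

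**No shared seasonal term, go-live 4 July 2022, effect at the end of year three:**

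| True shape | August start | October start | December start |
|---|---|---|---|
| No effect | 0 | 0 | 0 |
| Immediate 5% | −5.0% | −5.0% | −5.0% |
| Ramp over 12 months, then flat | −6.1% | −6.1% | −6.1% |
| Linear over 3 years | −5.0% | −5.0% | −5.0% |
| Standard error (points) | 9.7 | 12.9 | about 18.6 |
| Rise in deviance, any shape | – | 432 | 540 |

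(The ramp gives −6.1% because a straight line overshoots a ramp that flattens.) Neither the estimate nor the loss of fit depends on the shape.

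**With two shared annual harmonics, August to December start.** Two sets of assumptions were tried for a July go-live. In one, no effect moves from 0 to −6.8%, the step from −5.0 to −11.6%, the ramp from −6.6 to −13.0% and the linear effect from −5.0 to −11.5%. In the other, no effect moves from 0 to −5.0%, and step and linear both from −5.0 to −9.8%. With a late-September go-live the sign reverses: no effect moves from 0 to +11.3% and the step from −5.0 to +6.0%.

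**Phase-in before switch-on.** Let the effect build to −5% between 1 November 2021 and 4 July 2022, with no season. The three-year *average* estimate is then +9.0, +11.3 and +11.8% for August, October and November starts, while the no-effect, step and linear estimates do not move. So the check does respond, but by only 11.8 − 9.0 = 2.8 points. Goodness of fit is no better guide. With a lockdown drop of only 0.05 on the log scale, a late-September go-live and a true phase-in from November, the November start still fits worse than August (deviance 5.84 against 0.17). Keeping the August break and adding November as a fifth segment brings it to 0.00.

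**What the fourth segment can show.** With the August break kept, an immediate 5% effect appears as level ln 0.95 = −0.051 and slope 0. A linear one appears as level 0 and slope −0.0513/3 = −0.017 a year. If the counterfactual were known exactly, the misfit chi-square for a slope-only model under a true step would be 380 × 156 × 0.0513² × (1 − 3/4) ≈ 39. For a step-only model under a true linear effect it would be 380 × 156 × 0.0513² × (1/3 − 1/4) ≈ 13. These are upper limits, since the counterfactual has to be estimated.

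**The case against.** The strongest reply is that gradual refers to implementation as well as to effect. Grants opened before charging began, and the check is tied to activity dates, so it may be meant as a test of when phase-in started. This partly stands: the estimate does move a little under phase-in before switch-on. But the sentence presents the check as a test of the effects of implementing the CAZ, and the abstract defines implementation as the point when charging goes live.

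A reader might infer that the plan moves post-lockdown weeks into the lockdown segment. The text does not say so. It follows only if the four segments stay contiguous and a late-2021 start is chosen. Excluding those weeks left the no-effect, step and linear estimates unchanged, even with shared harmonics. An activity that began before August 2021 would do the opposite and bring lockdown weeks into the third segment. If the altered segment were extended past switch-on, it would bear on shape, but the plan defines it as ending there.

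A reader might also infer that the gradual assumption has no other check, or that the primary estimate is compromised. The document does not support either. The main model fits changes in both level and trend, further sensitivity analyses and lagged effects are planned, and the analysis is run at 12 months and again at three years.

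**Conclusion.** The point holds for this one sensitivity analysis. As stated, it cannot distinguish an immediate from a gradual effect after switch-on. That follows from the segment definitions and needs no assumed figure. On phase-in before switch-on it is weakly informative.

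The contamination is conditional on contiguous segments, a late-2021 start and a shared seasonal term. Under the assumptions tried it moved the estimate by roughly 5 to 7 points downwards or 11 to 12 points upwards, at least as large as the planned 5% effect. Size and sign depend on the assumed season, lockdown drop and go-live date, so these are illustrations and not predictions. This is not a detail left to a fuller document: the article fixes a method for a stated purpose that the method cannot serve. Because Analysis methods and Follow-up expect different shapes, a valid check is needed.

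**What to change.** - Keep the August 2021 change point fixed in every analysis.
- Enter activity start dates, such as the opening of grants, as additional change points, and describe that analysis as a check on phase-in before switch-on. The counterfactual then rests on a shorter last segment, so its standard error rises (in the fits without season, from 9.7 to 12.9 or about 18.6 points); it should stay secondary.
- Test gradualness within the post-switch-on segment by comparing prespecified forms: step only, slope only, and a ramp to 12 months then flat, which matches the compliance timing in Follow-up. Report the three-year effect under each.
- Reconcile the expected shape in Analysis methods with that in Follow-up.

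The cost is a sentence or two of text and a few extra model fits, with no new data collection.
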